**FIGURE 3 cnr270242-fig-0003:**
[figure not shown]
Gating strategy for the identification of the B cell subpopulations. Lymphocytes will be selected in the FSC‐A versus SSC‐A plot, then only singlets (SSC‐H vs. SSC‐A) and viable cells (negative for L/D in L/D vs. SSC‐A plot) will be taken into consideration for the analysis. For tissue samples, CD45^+^ (CD45 vs. SSC‐A) cells will be selected, while in blood samples this marker will not be used, directly selecting B cells for their positivity for CD19 (CD19 vs. SSC‐A). Among B cells, different subtypes will be analyzed, as extensively described in the text. The gating strategy will be manually drawn by an expert flow cytometrist and applied to all samples.

The data on immune cell numbers and phenotypes obtained from cytofluorimetric analysis of the digested biopsies will be confirmed by histological evaluation of the presence of tumor‐infiltrating B, T, and mast cells in the samples from the same patient. As reported in Figure 4 histological images of immune cells infiltrating the TME of a representative HGSOC subject show detectable CD4^+^ and CD8^+^ T cells as well as CD20^+^ B cells that are mostly peritumoral and organized in lymphocyte aggregates. Tryptase+ mast cells are also evident and appear focally distributed at tumour periphery.

**FIGURE 4 cnr270242-fig-0004:**
[figure not shown]
Example of immunohistological identification of immune markers in HGSOC. (A) Hematoxylin and eosin (H&E) staining and Cytokeratin‐7 (CK7) immunohistochemistry of peritoneal biopsy of one representative HGSOC patient. (B) Representative immunohistological images used to identify CD4+ T cells, CD8+ T cells, CD20+ B cells, and tryptase+ mast cells in the TME of the same representative HGSOC patient. All images taken at 5× magnification; 200 μm scale bar.

The histological analysis will serve to corroborate the data obtained from the cytofluorimetric analysis, while also providing information on the spatial distribution of immune cells in the tissue and potentially providing insight into the co‐localization of B and mast cells in the tumor. Our preliminary observations showed the presence of tertiary lymphoid structures in patients with a high CRS score after NACT (data not shown), suggesting the active role of the lymphoid response in patients. Furthermore, double staining for mast cell tryptase and specific cytokines (TNF‐α, IL‐17, IL‐10, …) will be performed to characterize the number and distribution of mast cells in the TME as well as their activation state. The number of mast cells and their cytokine profile will be correlated with tumor grade (according to the FIGO scoring system) and response to NACT. These observations will determine whether mast cells possess a plastic phenotype dependent on the inflammatory environment and will shed light on the functions of MC in OC progression.

The in vitro expanded PDOs will be studied to identify molecular changes common to all analyzed ovarian tumors and/or unique to each individual patient. Briefly, the mutational status of the PDO will be compared to that of the corresponding tumor tissue; then PDO cultures will be evaluated for the expression of markers of ovarian tissue (cytokeratin 7, PAX8, and WT‐1) by immunohistochemistry or confocal microscopy. Moreover, organoids' susceptibility to drugs (Carboplatin and Parp‐I Olaparib) will be estimated through the CellTiter‐Glo 3D Cell Viability Assay. Eventually, co‐cultures of PDO and B cells (isolated from peripheral blood) or mast cells (using LAD2 or HMC‐1 mast cell lines) will be set up to investigate how the presence of B cells or mast cells influences the PDO response to drugs.

Aliquots of PDOs, circulating or infiltrating immune cells and/or RNA isolated from them will be preserved for gene expression studies. Culture supernatants will be kept at −80°C for metabolite detection (Figure 5).

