**FIGURE 1 cnr270242-fig-0001:**
[figure not shown]
Flowchart of MICO trial. t is expressed in months. NACT = neoadjuvant chemotherapy; TME = tumor microenvironment.

Clinical data collection of HGSOC patients will include age, menopausal status, Body Mass Index (BMI), BRCA mutational status, history of breast cancer, preoperative CA125, type of surgery, predictive index (PI) score, 2014 FIGO stage [25] and residual tumor.

All HGSOC patients will be triaged for staging laparoscopy (LPS) to obtain a histological diagnosis and to provide tumor load assessment through the PI score. The intraoperative evaluation will consist of histological diagnosis of HGSOC at frozen section and verification of diffusion intras‐abdominal disease.

Patients with LPS‐PI < 10 will undergo open primary debulking surgery (PDS); if PI was ≥ 10, patients were referred to neoadjuvant chemotherapy [26, 27].

After 3–4 cycles of neoadjuvant chemotherapy (NACT), in the presence of reduced tumor load, patients will undergo interval debulking surgery (IDS). During IDS, peritoneal biopsies will be collected at the time of surgery (*t* = 3) and fresh tissue samples will be sent to the Department of Medicine, University of Udine.

The pathologist will evaluate the chemotherapy response score (CRS), a three‐level pathological response scoring system on omental specimens, which can predict prognostic outcomes in patients with advanced epithelial OC undergoing neoadjuvant chemotherapy [28, 29].

At *t* = 0 and *t* = 3, the removed tissue will be sent to the Pathology Department, where it will be selected by the pathologist, who will collect a fragment of tumor tissue and will divide it into three parts: one for the identification of cells composing the TME (through multiparameter cytofluorimetric analysis), one for histological diagnosis, and one for organoid generation.

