**FIGURE 5 cnr270242-fig-0005:**
[figure not shown]
Experimental steps of MICO trial (created with Biorender.com).

Six months after surgery (*t* = 6), and at subsequent 6‐month intervals (*t* = 12, *t* = 18, *t* = 24, and *t* = 36), patients will undergo regular follow‐up according to the clinical protocol. In case of recurrences requiring further surgical intervention, TME and blood will be reanalyzed, and new PDOs cultures will be generated. The phenotype of immune cells infiltrating the tumor and PDOs reactivity will be compared to those obtained at *t* = 0. This will make it possible to monitor changes over time in the composition of TME and the behavior of the PDOs.

Participation in the study will be requested during scheduled visits to the Obstetrics‐Gynecology Department of ASUFC or during outpatient visits. All data obtained during the study will be processed and treated exclusively in pseudo‐anonymized form for research purposes and will not be used for other purposes. Each collected sample will be coded with a progressive number.

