## Discussion

3

The knowledge of TME, integrated with genetic and molecular features, could help to better understand the OC behavior. In recent decades, considerable effort has been dedicated to understanding the role of immune cells in OC, with particular attention paid to T cells and macrophages. However, therapies targeting T cells (such as those which act on the PD1, LAG3 or TIGIT pathways) have yielded limited success in OC so far [35] suggesting that other immune cells or other pathways might play a pivotal role in this type of tumor.

Among cells under investigation, B cells and mast cells could represent putative crucial cells able to influence the TME. Beyond their antibody‐mediated functions, B cells can act as antigen‐presenting cells influencing T cell activation, can interact with innate immune cells modulating the immune responses in both beneficial and detrimental ways, and can produce mediators with inflammatory or immunosuppressive functions [36].

Similarly, a growing body of literature supports the key role of mast cells, primarily well known for their role in IgE‐mediated allergic response, in tumor progression in a variety of cancers, making them a highly attractive therapeutic target for a wide range of malignancies [37]. However, the data available in the context of gynecological malignancies are mostly controversial, sustaining both pro‐tumoral [38] and anti‐tumoral effect of mast cell on OC [17].

For these reasons, the MICO project aims to identify the main populations of immune cells in the TME and characterize in detail the role of B and mast cells in HGSOC patients by monitoring their accumulation and their phenotype among different patients, in relation to disease progression (FIGO stage) and in response to NACT. In parallel, PDO co‐cultures will be used as an in vitro model to study the effects of B lymphocytes and mast cells on cell growth and drug response. The in vitro data will be compared with patient response to therapy. This information could have both prognostic and therapeutic relevance. Some patients may have tumors with specific TME features that may influence the aggressiveness or treatment response of the tumor itself. From a personalized medicine perspective, the better knowledge of TME could tailor the treatment and management of OC to the unique characteristics of the specific patient's tumor.

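### Correlating mast-cell features with FIGO classification and NACT response shows whether patients differ, not whether mast cells change, so it cannot settle plasticity

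*Protocol article*

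**What the plan says.** All of this is in the protocol article.

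- **The analysis.** Section 2.1 (text after Figure 4) describes double staining for tryptase and cytokines, and then states that the "number of mast cells and their cytokine profile will be correlated with tumor grade (according to the FIGO scoring system) and response to NACT".
- **The conclusion.** The next sentence reads: "These observations will determine whether mast cells possess a plastic phenotype dependent on the inflammatory environment".
- **The unit of comparison.** Section 3 (Discussion) restates the aim as "monitoring their accumulation and their phenotype among different patients, in relation to disease progression (FIGO stage) and in response to NACT".
- **The response measure.** Section 2.1 has the pathologist score CRS, a three-level "pathological response scoring system on omental specimens". I take this to be the NACT response meant in the correlation.
- **Repeat tissue.** For neoadjuvant patients who reach interval debulking surgery (IDS), section 2.1 says: "During IDS, peritoneal biopsies will be collected at the time of surgery" (t = 3). At both t = 0 and t = 3, one part of the tissue goes to histology.
- **The within-patient comparison that is stated.** Section 2.1 (text after Figure 5) says: "In case of recurrences requiring further surgical intervention, TME and blood will be reanalyzed". It adds: "The phenotype of immune cells infiltrating the tumor and PDOs reactivity will be compared to those obtained at" t = 0. This is not linked to the plasticity sentence.

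**The concern.** A plastic phenotype is one that changes with its surroundings. A correlation across patients has as its null hypothesis that patients who differ in FIGO class or response do not differ in their mast cells. That null can be false when nothing changes in anyone, and it can be true when something changes in everyone. Here a stated analysis is tied to a stated conclusion that does not follow from it, so a fuller statistical plan could add tests but would not make this sentence correct.

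What is at stake is how a secondary result is read. Mast cells are a declared focus of the study. A significant correlation could be published as evidence that mast cells adapt to the tumour, and a null one as evidence that they do not. Neither reading would be justified.

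**Working it through.** The plan gives no figure on this point, so there is none to reproduce. The check is algebraic, with simulations as illustration.

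**Model.** Let the mast-cell feature of patient i be m(i,0) = z(i) + e at t = 0 and m(i,3) = z(i) + d(i) + e at t = 3. Here z is the patient's stable level, d is the true change and e is independent noise. Let R(i) be the patient's response.

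- Cross-sectional correlation at t = 0: driven by Cov(z, R). The change d does not enter.
- Cross-sectional correlation at t = 3: driven by Cov(z, R) + Cov(d, R). The two terms cannot be separated from one value per patient.
- Paired difference m(i,3) − m(i,0): its mean estimates the mean of d, and z cancels.

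**Case A, no change but a prognostic profile.** With d = 0 and Cov(z, R) not zero, the correlation is non-zero and would be read as plasticity. The paired mean is zero.

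**Case B, the same change in everyone.** With d constant, Cov(d, R) = 0. If z is also unrelated to R, both correlations are zero although every patient changed. The paired mean is d.

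**Illustration.** The two-tailed 0.05 level is from section 2.11. The sizes 43 (Abstract) and 93 (section 2.4) are both in the article, but it does not say how many patients will have both biopsies. All other inputs are assumptions: stable level with SD 1, noise SD 0.5, correlation 0.4 in Case A, shift 0.5 SD in Case B.

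| Case | n | Correlation significant | Paired t-test significant |
|---|---|---|---|
| A | 43 | 67% | 5% |
| A | 93 | 95% | 5% |
| B | 43 | 5% | 99% |
| B | 93 | 5% | 100% |

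A hand check agrees:

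- Case A: noise attenuates the correlation to 0.4/√(1 + 0.25) = 0.358, and atanh(0.358) = 0.374. For n = 43, 0.374 × √40 − 1.96 = 0.41, or about 66% power. For n = 93, 0.374 × √90 − 1.96 = 1.59, or about 94%.
- Case B: the difference has SD √2 × 0.5 = 0.707, so the standardised shift is 0.5/0.707 = 0.707. For n = 43, 0.707 × √43 − 1.96 = 2.68, or over 99%.

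**Sensitivity to the assumptions.** With 30 to 60 pairs, a three-level response, rank tests and noise SD 0.3, Case A correlations of 0.3 to 0.5 are significant in 28% (n = 30, 0.3) to 93% (n = 60, 0.5) of runs, and the signed-rank test stays near 5%. In Case B the signed-rank power depends strongly on noise:

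| Noise SD | n = 30 | n = 45 | n = 60 |
|---|---|---|---|
| 0.5 | 96% | 99% | over 99.9% |
| 0.8 | 63% | 81% | 91% |
| 1.0 | 46% | 63% | 76% |

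The direction is the same throughout. The size depends on the chosen inputs.

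**The case against.** The strongest reply has five parts.

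1. **Plasticity is not a listed endpoint.** Section 2.3 does not name it among the primary, secondary or exploratory endpoints, and the sample size does not depend on it. This stands, and it limits the weight of the point.

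2. **A condensed article may leave a paired test to the full protocol.** This also stands. A reader might infer that the study has no within-patient data or plans no paired analysis. The article does not support that: tissue is taken at t = 0 and t = 3, immune phenotype at recurrence is compared with t = 0, and section 2.11 names a Wilcoxon test without saying whether it is rank-sum or signed-rank. The point is not that a test is absent, but that the stated correlations are given a conclusion they cannot carry.

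3. **The text may not be purely between-patient.** Section 2.1 does not say which time point is correlated, the Discussion phrase on response to NACT could mean before and after, and the observations referred to could include the staining itself. This is a fair ambiguity. However, the only analysis stated is a correlation with patient-level variables, and the Discussion says the comparison is among different patients.

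4. **Plastic may be meant loosely, as varying between tumour environments.** Then association is the right word. Neither FIGO class nor response to NACT is itself a measure of inflammation, so even that dependence is seen only indirectly.

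5. **A paired comparison would not prove plasticity.** This is correct. A reader might infer that moving the conclusion to the paired test solves the problem. It does not: the change from t = 0 to t = 3 mixes phenotype switching with recruitment of different mast cells, direct chemotherapy effects and differences in biopsy site, and the Discussion itself names heterogeneity of the microenvironment as a limit. Mast-cell number measures abundance, not phenotype.

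**Conclusion.** The point holds in a limited form. As stated, the correlations can show that mast-cell features are associated with FIGO class or response to NACT. They cannot determine whether the phenotype is plastic, and the conclusion could be wrong in either direction. This follows from the structure of the comparison and needs no assumed effect size.

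No error rate can be attached. The simulated percentages must not be read as the study's false-positive or false-negative rates: Case A is the power to detect a real association, and the 5% in Case B follows from making response independent of the profile.

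A paired t = 0 to t = 3 comparison is the more direct evidence on change, but it should not be said to determine plasticity either. It covers only neoadjuvant patients who reach interval surgery, which section 2.1 makes conditional on reduced tumour load, and who have evaluable tissue at both times. The primary endpoint, concordance of organoid and clinical platinum sensitivity, is not affected.

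**What to change.** - In section 2.1, report the correlations with FIGO class and response to NACT as associations, and delete the statement that they determine plasticity.
- Add a paired comparison of the cytokine-positive mast-cell fraction at t = 0 and t = 3 (Wilcoxon signed-rank) in neoadjuvant patients with both biopsies. Report mast-cell number separately as abundance. Relate the within-patient change to CRS.
- Describe the paired result as evidence of change in the mast-cell compartment over NACT, and list what it cannot separate: chemotherapy effect, recruitment of different mast cells and biopsy site. State how many patients contribute pairs.

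The cost is a few sentences and one analysis on tissue the study already plans to take. The article does not say at which time points the double staining is done, so some extra staining may be needed. The analysis will not describe patients who have primary surgery or who do not reach interval surgery.

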**FIGURE 5 cnr270242-fig-0005:**
[figure not shown]
Experimental steps of MICO trial (created with Biorender.com).

Six months after surgery (*t* = 6), and at subsequent 6‐month intervals (*t* = 12, *t* = 18, *t* = 24, and *t* = 36), patients will undergo regular follow‐up according to the clinical protocol. In case of recurrences requiring further surgical intervention, TME and blood will be reanalyzed, and new PDOs cultures will be generated. The phenotype of immune cells infiltrating the tumor and PDOs reactivity will be compared to those obtained at *t* = 0. This will make it possible to monitor changes over time in the composition of TME and the behavior of the PDOs.

Participation in the study will be requested during scheduled visits to the Obstetrics‐Gynecology Department of ASUFC or during outpatient visits. All data obtained during the study will be processed and treated exclusively in pseudo‐anonymized form for research purposes and will not be used for other purposes. Each collected sample will be coded with a progressive number.

### Participants

2.2

Eligibility criteria are described in Table 1. The MICO study will enroll patients with advanced HGSO cancer.

**TABLE 1 cnr270242-tbl-0001:** MICO study inclusion and exclusion criteria.

Inclusion criteria	Exclusion criteria
Patients ≥ 18 and < 80 years old	Patients < 18 or > 80 years old
Pathologic diagnosis of HGSOC	Ongoing or suspended immunosuppressive therapy within the last 6 months
FIGO Stages III–IV	Congenital or acquired immunodeficiency
Patient having signed the consent to participate in the study	Immunosuppressive state
	BMI > 30
	Chemotherapy for another malignancy in the last 12 months
	Diagnosis of HGSOC without surgery

The control group will include women who underwent risk reduction bilateral salpingo‐oophorectomy and peritoneal biopsies due to genetic predisposition to OC. Exclusion criteria will be the same as for HGSO patients, excluding the diagnosis of HGSOC. Women with a diagnosis of occult peritoneal, ovarian, or tubal cancer and serous tubal intraepithelial carcinoma on definitive pathologic examination will also be excluded.

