### Study Objectives and Endpoints

2.3

The primary endpoint of the MICO study will be to evaluate the concordance between in vitro platinum‐based chemotherapy sensitivity and in vivo sensitivity.

In more detail:
Organoids generation in vitro system to evaluate tumoral cells' response to carboplatin treatment.Patient's clinical response monitoring. We will record platinum‐free interval (defined as interval expressed in months between the last dose of platinum‐based chemotherapy and the recurrence or progression of the disease), progression‐free survival (calculated from the first surgery until the first disease progression or the last follow‐up) and overall survival (defined as the length of time from the date of first surgery to death or the date last seen). The disease recurrence or progression will be evaluated according to RECIST1.1 [32]. Relapsed patients will be divided according to response to platinum treatment as resistant (platinum‐free interval 1–6 months of last platinum cycle) and partially platinum‐sensitive/platinum‐sensitive (platinum‐free interval > 12 months).

The model will be considered concordant if PDOs of platinum‐resistant patients will be viable on day 5 after carboplatin addition and if PDOs of platinum‐sensitive/partially platinum‐sensitive patients will not be viable (see Section 2.8).

The secondary endpoints will be:
Characterize the composition of the immune TME in order to understand if there are differences between tumor‐infiltrating immune subpopulations among patients, differences that could be predictive of early recurrence and/or different responses to therapy, focusing on immune populations still poorly studied (such as B cells for acquired immunity and mast cells for innate immunity).Organoids generation in vitro system to evaluate tumoral cells' viability in response to PARP‐I treatment.Association of TME composition, organoid response to drugs, and clinical evidence to identify predictors of response to therapy.To compare the TME of HGSOC patients with the TME of the control group.To develop a platform that allows in vitro analysis of the tumor followed by the identification of personalized therapy for each patient and, in case of recurrence, to monitor over time changes in the composition and responsiveness of the patient's TME.

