### Sample Size

2.4

The sample size was calculated in order to evaluate the concordance between in vitro platinum‐based chemotherapy sensitivity and in vivo sensitivity.

From literature, this concordance is 0.80 with traditional patient‐derived xenografts [33]; we expect a concordance of 0.95 using PDOs [34]. A sample size of 93 patients will allow us to detect a true value of Cohen's Kappa of 0.95, with a power of 80% and an allocation of the two groups of 1:1.

Ninety‐three control patients will also be enrolled to compare the number of CD45+ cells at baseline. This sample size will allow estimating an effect size of CD45+ cell number of less than 0.3 between the control and case groups, with an alpha of 5% and power of 80%.

[32, 33].

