### Statistical Methods

2.11

The sample will be described in its characteristics using descriptive statistical techniques. Quantitative variables will be summarized with mean, standard deviation, minimum, and maximum. Qualitative variables will be described with frequency tables (absolute and percentages).

We will record platinum‐free interval, progression‐free survival, overall survival, and sensitivity to platinum‐based chemotherapy.

A univariate and multivariate Cox analysis will be implemented to explore factors associated with progression‐free survival. The proportional hazard assumption will be tested using the Schoenfeld residual test. Multivariable analysis will be corrected for potential confounding factors. Survival curves will be obtained using Kaplan–Meier analysis. All statistical tests will use a two‐tailed significance level of 0.05. The *χ*
^2^ test or Fisher's exact test will be used to analyze the distribution of variables according to different subgroups. The non‐parametric Wilcoxon test will be used to analyze the distribution of continuous variables.

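### The case-control comparison of the tumour microenvironment is planned without balancing or adjustment for age and menopause, and genetic predisposition is tied to group by the choice of controls

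*Protocol article*

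**What the plan says.** All references are to the protocol article.

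- **Controls (2.2 Participants).** Controls are women having risk-reducing bilateral salpingo-oophorectomy and "peritoneal biopsies due to genetic predisposition to OC".
- **Comparability (2.2).** "Exclusion criteria will be the same as for HGSO patients, excluding the diagnosis of HGSOC". Both groups therefore have essentially the same age limits (for cases, "Patients ≥ 18 and < 80 years old") and the same bars on BMI above 30, immunosuppression and chemotherapy for another malignancy in the last 12 months. No matching, stratification or frequency balancing is stated.
- **Cases (2.2, Table 1).** BRCA status is not an eligibility criterion.
- **Variables (2.1 Trial Design).** "Clinical data collection of HGSOC patients will include age, menopausal status, Body Mass Index (BMI), BRCA mutational status, history of breast cancer", followed by tumour and surgical items. No corresponding list is given for controls.
- **Use of the controls.** A secondary endpoint in 2.3 is "To compare the TME of HGSOC patients with the TME of the control group". In 2.4 Sample Size, ninety-three "control patients will also be enrolled to compare the number of CD45+ cells at baseline", with a stated aim of "estimating an effect size of CD45+ cell number of less than 0.3 between the control and case groups".
- **Analysis (2.11 Statistical Methods).** The non-parametric "Wilcoxon test will be used to analyze the distribution of continuous variables". Correction for confounding is mentioned once, directly after the Cox model for progression-free survival.

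**The concern.** Two groups chosen by different routes into surgery may differ in more than the presence of a tumour. One group has advanced cancer and the other has preventive surgery because of an inherited risk. The shared age range is about 62 years wide (18 to 80), so the same limits can hold quite different age and menopausal distributions.

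The confounder correction in 2.11 cannot reach this comparison where it stands, because controls have no progression-free survival. A Wilcoxon test takes no covariates.

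At stake is the interpretation of one secondary endpoint and of the 93 controls enrolled for it. A difference in CD45+, B-cell or mast-cell content might be read as a tumour effect when part or all of it reflects age, menopausal status, inherited predisposition or earlier breast cancer treatment. The chemotherapy exclusion covers only the last 12 months, and the 2.1 list names breast cancer history but not its treatment.

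**Working it through.** **1. The plan's own figure.** Section 2.4 gives 93 per group, alpha 5%, power 80%, effect size below 0.3; 2.11 makes tests two-sided. For two independent groups the detectable standardised difference is (1.960 + 0.842) × √(2/93) = 2.802 × 0.1466 = 0.41. Detecting 0.3 would need 2 × (2.802/0.3)² ≈ 175 per group, and 93 per group has 53% power at 0.3. The stated figure fits only 1:1 matched pairs (2.802/√93 = 0.29), a design the article does not describe. This is a separate matter, and I take 0.41 as the baseline below.

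**2. Bias of an unadjusted comparison.** The article gives no age distribution for either group and no age-marker correlation, so both are assumptions. Let D be the case-control age gap in within-group SDs and r the within-group correlation of age with the immune marker. With no tumour effect, the spurious standardised difference is D × r. With standard error √(2/93) = 0.1466, the chance of a significant result is Φ(Dr/0.1466 − 1.96) + Φ(−Dr/0.1466 − 1.96). This is a normal approximation; a Wilcoxon test behaves similarly.

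| D (SD) | r = 0.1 | r = 0.2 | r = 0.3 |
|---|---|---|---|
| 0.5 | 6.3% | 10.5% | 17.6% |
| 1.0 | 10.5% | 27.6% | 53.4% |
| 1.5 | 17.6% | 53.4% | 86.6% |

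Example: D = 1.0 and r = 0.2 give 0.20; 0.20/0.1466 = 1.364; Φ(−0.596) + Φ(−3.324) ≈ 0.276. At D × r = 0.30 the spurious difference equals the effect size named in 2.4.

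**3. Cost of adjusting for age.** With equal groups, the variance of the group effect is inflated by 1 + D²/4. The detectable difference becomes 0.411 × √(1 + D²/4). Holding it at 0.41 needs 93 × (1 + D²/4) per group.

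| D (SD) | Inflation | Detectable difference | n per group to hold 0.41 |
|---|---|---|---|
| 0.5 | 1.0625 | 0.42 | 99 |
| 1.0 | 1.25 | 0.46 | 117 |
| 1.5 | 1.5625 | 0.51 | 146 |

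This ignores the small gain from the age-related variance that the model removes, so it slightly overstates the loss.

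**4. Predisposition.** Every control is predisposed. A non-carrier case has no control of the same genotype, so no model fitted to the whole sample can estimate a tumour effect free of predisposition without extrapolating. Carrier cases can be compared with controls, because BRCA status is recorded for cases. The carrier share is not given. If it were 15%, 20% or 30% of 93 (about 14, 19 or 28 cases), the detectable difference against 93 controls would be 2.802 × √(1/n + 1/93) = 0.80, 0.70 or 0.60. At 20%, power for a difference of 0.41 is about 37% (0.41/0.252 − 1.96 = −0.33).

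**The case against.** The strongest reply is that this is a condensed article. Control data fields and adjustment of a secondary comparison usually sit in the full protocol or analysis plan, which are not shown. The 2.1 list describes cases; it does not say that nothing is collected on controls. The Wilcoxon sentence is generic and is not assigned to the case-control comparison as its only analysis. The shared exclusions give real comparability on BMI above 30, immunosuppression and recent chemotherapy. Age and BMI must be checked in controls to apply those exclusions, so the values will exist.

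Much of this stands, and if the full protocol already lists control covariates and an adjusted analysis, that part of the fix is met. What remains is that the choice of control group is fixed here, that the shared criteria do nothing for age within the permitted range or for menopause, and that an analysis plan cannot adjust for variables nobody recorded.

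A reader might infer that the comparison can never separate tumour from age, menopause and BRCA status, so that the endpoint is unanswerable. The documents do not support that. Age and menopause are repairable by recording and adjusting. Only predisposition is structural, and only where cases are non-carriers. Section 2.3 promises a comparison, not a causal attribution.

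Nor do the larger percentages above show that serious bias is present. The lowest corner of the assumed range, 6%, is close to nominal.

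**Conclusion.** The point holds in limited form. Followed as written, the case-control comparison is open to confounding by age and menopausal status, and is inseparable from predisposition for non-carrier cases. Whether the bias is negligible or large cannot be said from the article. The range of about 6% to 87% rests wholly on assumed age gaps and correlations, and the direction is unknown. One secondary endpoint and the purpose of the control group are touched; the primary organoid concordance is not. The change should be made while enrolment is still to come or under way, when control variables can be collected prospectively.

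**What to change.** - **2.1:** extend the clinical data list to controls: age, menopausal status, BMI, predisposition gene, and breast cancer history. Add breast cancer treatment in both groups.
- **2.11:** make the case-control analysis of CD45+ and immune subsets a regression on group adjusted for age and menopausal status, on a transformed or rank scale if needed. Keep the Wilcoxon test as the unadjusted companion.
- **2.11:** add mutation-positive cases v controls as a descriptive sensitivity analysis with confidence intervals. It should not be a condition for concluding, because with few carriers it would often miss a real difference. Predisposition is also a wider term than BRCA, so this restriction aligns the groups only in part.
- **2.2 or the limitations in section 3:** state that predisposition cannot be adjusted for across the whole sample.

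**Cost:** a few chart variables, one adjusted and one descriptive analysis, and a modest loss of precision (detectable difference from about 0.41 to between 0.42 and 0.51 over the assumed age gaps). Holding precision at 0.41 would need more participants, as shown in the working. Selecting controls by age band or menopausal status would help further, but at a single centre it trades against accrual, so I would leave it optional.
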